### Statistical Analysis

Data will be analyzed using IBM SPSS Statistics software (version 29.0), adhering to the intention-to-treat principle, which includes all randomized participants regardless of protocol adherence. Participant characteristics and baseline measures will be summarized using descriptive statistics, including mean, SD, median, and IQR.

Before primary analyses, data will be assessed for normality using the Shapiro-Wilk test and homogeneity of variance using the Levene test. For outcomes meeting parametric assumptions, a 2-way mixed model ANOVA will be used to compare the effects of the interventions’ interactions between and within groups. Appropriate transformations or nonparametric alternatives will be applied in cases of violated parametric assumptions. Potential confounding variables, such as baseline motor function and stroke severity, will be included as covariates to provide adjusted treatment effect estimates. Statistical significance will be set at *P*<.05 for all analyses.

The linear mixed-effects models that include the center as a fixed effect covariate and random intercepts at the participant level will be used to address residual center-specific effects without invoking a design effect. This modeling framework accommodates hierarchical data structures in single-cluster designs while preserving valid inference for group-by-time interactions.

Missing data will be addressed using multiple imputation techniques, with sensitivity analyses comparing results to those obtained using the baseline observation carried forward method. This comprehensive approach ensures a robust interpretation of intervention effects while preserving statistical power.

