## Introduction

### Background

Stroke is one of the most debilitating brain disorders, often leading to death or severe functional impairment. The global burden of stroke is exceptionally high in low- and middle-income countries, where increased incidence, mortality, disability, and economic strain are prevalent [1]. Stroke is the second leading cause of death and disability worldwide [2], with over 116 million healthy years lost annually due to disabilities and fatalities associated with stroke [3]. Among stroke survivors, more than 80% experience motor impairments in the upper extremities (UEs) [4], significantly limiting their ability to engage in social and daily activities. While approximately two-thirds of patients who have experienced a stroke can walk independently 6 months after the stroke, nearly half remain unable to functionally use the affected arm despite receiving treatment [5].

UE impairment is a common challenge for stroke survivors, often leading to significant motor dysfunction and impacting daily living activities [6,7]. Improving UE function through targeted rehabilitation is essential for enabling stroke survivors to perform daily tasks independently [8,9]. Constraint-induced movement therapy (CIMT) is a highly effective intervention for enhancing UE function after stroke [10] and is considered one of the most essential rehabilitation approaches for stroke recovery [11]. Numerous systematic reviews provide strong evidence supporting CIMT’s use across acute, subacute, and chronic phases of stroke rehabilitation [12-15]. Consequently, CIMT is recommended as a core intervention in clinical guidelines worldwide, including in the United Kingdom [16], Australia [16], and Canada [17]. In addition, research indicates that CIMT can enhance functional performance compared to traditional rehabilitation and increase the use of the most affected UE [18].

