### Sample Size Calculation

We used the G*Power software (version 3.0.10; University of Düsseldorf) to calculate the required sample size. A mixed model ANOVA, a statistical method used to analyze the effects of interventions over time and between groups, was selected to analyze the interventions’ time, group, and interaction effects. The *F* test (ANOVA repeated measures within and between interactions), a specific type of statistical test used in the mixed model ANOVA, was selected for this analysis. With a study power of 80%, an α level of .05, and an effect size of 0.25 (based on the primary outcomes from a previous CIMT study [47]), a minimum sample size of 42 participants (14 in each group) is required. If a group has more than 14 eligible participants, the first 14 to provide consent will be recruited based on the referral date. This first-come, first-served approach ensures transparency in participant selection while maintaining cluster integrity.

An intention-to-treat analysis, which includes all randomized participants, regardless of their adherence to the protocol or completion of the study, will be implemented for this RCT. Under this approach, all recruited participants will be included in the final analysis regardless of protocol adherence, withdrawal, or discontinuation. For participants who withdraw or discontinue the treatment, their baseline data will be used as exit data in the primary analysis. This conservative approach acknowledges the potential impact of missing data while maintaining randomization integrity. Sensitivity analyses using multiple imputation techniques, which are statistical methods used to handle missing data, will be conducted to assess the robustness of findings against different missing data assumptions. This analytical strategy aligns with CONSORT guidelines for reporting randomized trials and addresses potential selection bias that might occur with complete-case analysis.

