## Results

Funding for this study from RECUKM began in November 2023. Between January 2023 and May 2023, we drafted the initial ethics proposal and hired the research staff. Research ethics applications were submitted to the RECUKM from May 2023 to November 2023. We anticipate publishing the study results in 2025.

This study will evaluate the effectiveness of CIMT combined with NMES, CIMT alone, and conventional neurodevelopmental therapy in rehabilitating UE function in chronic stroke survivors. The findings could enable physiotherapists to develop innovative therapies to promote UE function and assist in identifying the most effective treatments for poststroke UE dysfunction. We hypothesize that CIMT combined with NMES will be more effective than the other 2 therapies in improving UE function among survivors of stroke.

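### The stated hypothesis is that CIMT+NMES beats both other arms, but the planned and powered test is a non-directional three-arm group-by-time F, which does not test that

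*Protocol article*

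**What the plan says.** **Hypothesis.** The Results section of the protocol article states: "We hypothesize that CIMT combined with NMES will be more effective than the other 2 therapies". Anticipated Findings, in the Discussion, repeats the superiority claim against CIMT alone and conventional therapy, for motor function and perceived use.

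**Planned test.** Statistical Analysis says that "a 2-way mixed model ANOVA will be used to compare the effects of the interventions’ interactions between and within groups", with one .05 threshold for all analyses. It names no contrast between CIMT+NMES and either other arm. The linear mixed model described there is also directed at group-by-time interactions.

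**Powered test.** Sample Size Calculation uses the F test for "ANOVA repeated measures within and between interactions". The inputs are given as "With a study power of 80%, an α level of .05, and an effect size of 0.25", the effect size being taken from an earlier CIMT study. The result is that "a minimum sample size of 42 participants (14 in each group) is required".

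**Prior evidence.** Background presents CIMT as already effective: "research indicates that CIMT can enhance functional performance compared to traditional rehabilitation".

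**The concern.** The hypothesis has a direction and two parts, so it fails if CIMT+NMES does not beat either one of the other arms. The interaction F has a different null: equal mean change in all three arms. That null is false as soon as CIMT outperforms conventional therapy, which the Background treats as supported by research. It is also false if CIMT+NMES does worse than CIMT.

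The effect size does not help, because it comes from a CIMT study. The effect for which the trial is sized could lie wholly between CIMT and control.

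What is at stake is the new question, whether NMES adds anything to CIMT. Clinical Implications and Future Directions ties clinical use to the combined intervention showing superiority, but the article gives no criterion for showing it.

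**Working it through.** **Inputs.** From Sample Size Calculation: f=0.25, α=.05, power 80%, N=42, 14 per arm. From Assessment of Outcomes: m=2 assessments (baseline and postintervention). Assumed, because not stated: pre-post correlation ρ=0.5, sphericity, independent participants, no center effect.

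**1. Reproduce the plan's figure.** For the within-between interaction, λ = f²·N·m/(1−ρ) = 0.0625 × 42 × 2 / 0.5 = 10.5, with df = (3−1)(2−1) = 2 and 42−3 = 39. Noncentral F power is 0.803. N=42 is the smallest total that reaches 80%, so the article's number is recovered. At ρ=0.3 power would be 0.65, and at ρ=0.7 it would be 0.96.

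**2. Express λ as arm gains.** In SDs of change, λ = n·Σ(δᵢ − mean δ)². Only the overall spread of the three gains matters, not which arm is ahead. For gains (control, CIMT, CIMT+NMES) = (0, d, d), the sum of squares is (2/3)d², so λ = 14 × (2/3) × d². Setting this to 10.5 gives d² = 1.125 and d = 1.06.

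**3. NMES adds nothing and CIMT works.** The F column is exact (noncentral F). The contrast column is simulated with 39 error df and requires both contrasts to favor CIMT+NMES at two-sided P<.05.

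| Common CIMT gain d | λ | F significant | Both contrasts succeed |
|---|---|---|---|
| 0.5 | 2.33 | 24% | 1.8% |
| 0.75 | 5.25 | 49% | 2.3% |
| 1.06 (f=0.25) | 10.5 | 80% | 2.5% |

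In the last row the F is significant and CIMT+NMES also has the largest observed mean gain in 40% of trials. If all three arms are equal, the F rejects in 5%.

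**4. CIMT+NMES is worse than CIMT.** With gains (0, 1.06, 0.70) the F is significant in 69% of trials, and both contrasts succeed in 0.2%.

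**5. NMES has a real benefit, with f held at 0.25.** The F stays at about 80% throughout.

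| Gains (control, CIMT, CIMT+NMES) | NMES benefit over CIMT | Both contrasts succeed |
|---|---|---|
| (0, 1.00, 1.11) | 0.11 | 5% |
| (0, 0.88, 1.18) | 0.30 | 12% |
| (0, 0.61, 1.22) | 0.61 | 34% |
| (0, 0, 1.06) | 1.06 | 67% |

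The F therefore behaves the same whether NMES adds nothing or 1.06 SD. The 80% in the sample size section does not carry over to the hypothesis.

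**The case against.** The strongest reply is that nothing in the article says a significant F will be read as superiority of CIMT+NMES. The Statistical Analysis section also promises adjusted treatment effect estimates, and pairwise comparisons after a three-arm ANOVA are routine detail that a full protocol or SAP may contain. This largely stands. The usual sequence, a significant F followed by a significant CIMT+NMES over CIMT contrast, gives 2.5% at gains (0, 1.06, 1.06), 1.9% at (0, 0.5, 0.5) and 0.2% at (0, 1.06, 0.70). That is essentially the same protection as the two-contrast rule, so the harm arises only if no contrast is run. With three arms, the F is also a legitimate gate before pairwise tests.

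The objective also covers all three therapies, so an overall three-arm test has a proper place.

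What the reply does not remove is the mismatch in the article itself. It states a two-part directional hypothesis and then fixes, as the planned and powered analysis, a test with a different null. That concerns what the document commits to, not merely a detail left out.

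A reader might infer that the plan gives false support for NMES in 80% of trials. The documents do not support that. The 80% requires both CIMT arms to exceed control by 1.06 SD of change at ρ=0.5, and it becomes false support only if someone reads the F as a superiority result.

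**Conclusion.** The point holds in a limited form. The group-by-time F, as planned and powered, does not test the stated hypothesis, and a significant F alone must not be taken as evidence for adding NMES. If NMES adds nothing, it is significant in about 24% to 80% of trials as the CIMT benefit runs from 0.5 to 1.06 SD of change. These figures rest on ρ=0.5, independent participants and no center effect.

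The N=42 arithmetic is not in dispute; what is wrong is treating it as power for the superiority claim. Under the same assumptions, power for that claim at f=0.25 runs from about 5% to 67% over the patterns of real NMES benefit examined.

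One limit applies to any version of the analysis. Recruitment and Randomization allocates one center to each arm, so every contrast between arms is also a contrast between centers. Meeting a two-contrast rule is necessary for attributing a difference to NMES, but not sufficient.

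**What to change.** - **Statistical Analysis:** base the superiority claim on two prespecified contrasts of change from the planned model, CIMT+NMES minus CIMT and CIMT+NMES minus conventional therapy. Claim superiority on a given outcome only if both favor CIMT+NMES at two-sided P<.05. The F may stay as a gate or an overall summary, with a statement that it is not in itself evidence for adding NMES.
- **Multiplicity:** because both contrasts must succeed, no alpha split is needed between them within one outcome. This does not cover multiplicity across the four outcomes, which needs its own rule.
- **Sample Size Calculation:** state that the 80% power applies to the overall F only, and that at f=0.25 both contrasts succeed in about 5% to 67% of trials depending on the pattern of arm gains.
- **Strengths and Limitations:** state that each contrast is confounded with center.

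**Cost.** The changes are wording, and the contrasts come from the same model. The real price is that superiority becomes harder to claim at N=42. For scale, 80% power for the CIMT+NMES over CIMT contrast alone at 0.61 SD of change would need about 43 per arm (3 × 43 = 129 in total), under the same assumptions. If the sample is not enlarged, the article should present the NMES question as one that the trial may well not settle.

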##### Motor Function Subscale of the Fugl-Meyer Assessment for Upper Extremity

The Fugl-Meyer Assessment (FMA-UE) will be used to assess motor function, coordination, and speed of the affected extremity, hand, and wrist after stroke. The FMA-UE is a well-established and reliable measure with excellent internal consistency [40,41]. In addition, it has been reported as a reliable and valid measure of poststroke upper limb motor impairment [42]. It assigns scores from 0 to 2 (0=cannot perform, 1=performs partially, 2=performs fully), with a total possible score of 66.

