### Assessment of Outcomes

A blinded assessor unaware of group allocations will conduct baseline and postintervention assessments to prevent bias. The assessor will be trained in standardized assessment techniques and cannot access baseline data during postintervention evaluations.

A single trained assessor will perform all assessments at the respective rehabilitation centers while remaining blinded to group allocation and treatment throughout the study. This assessor will travel between centers to ensure consistent assessment procedures.

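### Shapiro-Wilk and Levene pre-tests decide, outcome by outcome, whether the mixed ANOVA behind the sample size is used or gives way to an unspecified alternative

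*Protocol article*

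**What the plan says.** Under Statistical Analysis, before the primary analyses, "data will be assessed for normality using the Shapiro-Wilk test and homogeneity of variance using the Levene test". Outcomes that meet the assumptions go to a 2-way mixed ANOVA. For the others, "Appropriate transformations or nonparametric alternatives will be applied in cases of violated parametric assumptions". The same paragraph says that potential confounders, "such as baseline motor function and stroke severity, will be included as covariates", and sets P<.05 for all analyses.

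The next paragraph plans linear mixed-effects models with center as a fixed effect and participant random intercepts, aimed at group-by-time interactions. They are not tied to the pre-tests. They are not named as primary either.

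Under Sample Size Calculation: "The *F* test (ANOVA repeated measures within and between interactions), a specific type of statistical test used in the mixed model ANOVA, was selected". The inputs are: "With a study power of 80%, an α level of .05, and an effect size of 0.25". The result: "a minimum sample size of 42 participants (14 in each group) is required".

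There are two measurement times: "A blinded assessor unaware of group allocations will conduct baseline and postintervention assessments to prevent bias". Eligibility requires an FMA-UE score of at least 44, and the scale is described "with a total possible score of 66".

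**The concern.** The pre-test gate is written into the protocol itself. An analysis plan could name the fallback test, but the rule that significance tests on the trial data choose the method is already fixed here.

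- **The question can change.** The sample size supports a test of whether change differs between groups. A simple rank test on post scores compares final levels instead, and it cannot carry the promised covariates. Of four outcomes, some could be reported as adjusted group-by-time effects and others as unadjusted comparisons of final scores, depending on chance features of the data.
- **The gate is noisy.** With 14 participants per group, a normality test often misses real departures, and repeated over several cells it often rejects when nothing is wrong.
- **FMA-UE is bounded.** Entry at 44 and a maximum of 66 confine baseline scores to a cut range, so rejection can be common even if the residuals of the planned model are acceptable.

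**Working it through.** **1. The plan's own figure.** Inputs from Sample Size Calculation: f = 0.25, α = .05, 3 groups (k), N = 42; from Assessment of Outcomes: 2 times (m). For the within-between interaction, λ = f²·N·m/(1 − ρ), with (k − 1)(m − 1) = 2 and (N − k)(m − 1) = 39 degrees of freedom. The pre-post correlation ρ is not stated. With ρ = 0.5 assumed, λ = 0.0625 × 42 × 2/0.5 = 10.5, power is 0.803 and the minimum N is 42, so the figure is reproduced. Correlations of 0.3, 0.7 and 0.8 would give 60, 27 and 21.

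**2. Switching with perfectly normal data.** The section does not say whether the tests apply to cells, pooled data or residuals, or how many rejections count. Assume one Shapiro-Wilk test in each of the 6 group-by-time cells, one Levene test at each of the 2 times, level .05, and a switch on any rejection. Treated as independent, 1 − 0.95^8 = 0.337 per outcome. Simulation gives 32–37%.

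**3. Switching with bounded FMA-UE data.** The protocol gives no mean, SD or shape, so several assumed shapes on 44–66 were simulated. The cell-wise rule switched in 33–91% of trials. Group-centred residuals plus Levene gave 20–80%, and pooled Shapiro-Wilk at each time gave 15–99%.

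**4. What a switch costs.** With two times, the interaction F test equals a one-way ANOVA on change. Change has variance 2σ²(1 − ρ) and the post score has variance σ² (equal variances assumed). If the effect on change is held at the planned λ = 10.5, a post-score comparison has λ = 10.5 × 2(1 − ρ):

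| ρ | λ, post only | Power, ANOVA on post | Power, Kruskal-Wallis on post (simulated, bounded data) |
|---|---|---|---|
| 0.5 | 10.5 | 0.803 | 0.76–0.78 |
| 0.7 | 6.3 | 0.571 | 0.51–0.53 |
| 0.8 | 4.2 | 0.405 | 0.36–0.37 |
| 0.9 | 2.1 | 0.220 | 0.17–0.20 |

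Kruskal-Wallis on change scores gave 0.59–0.77 on bounded data, against 0.64–0.80 for the planned test, a loss of about 2–6 points.

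**5. The whole two-stage rule, normal data.** Weighting by the 0.337 switch rate as an approximation:

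- ρ = 0.7: 0.663 × 0.803 + 0.337 × 0.571 = 0.72
- ρ = 0.8: 0.663 × 0.803 + 0.337 × 0.405 = 0.67

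Simulation with Kruskal-Wallis on post scores as fallback agrees: about 0.72, and 0.65–0.67. At ρ = 0.5 there is no loss.

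**6. A different scaling.** If f = 0.25 is instead held on the raw-score scale, the planned test has λ = 5.25/(1 − ρ) and the post-score test keeps λ = 5.25/(1 − ρ) × 2(1 − ρ) = 10.5 at every ρ. At ρ = 0.7 the planned test then has power 0.96 (λ = 17.5), and the two-stage rule has about 0.663 × 0.96 + 0.337 × 0.80 = 0.91. Power is still lost, but it stays above 80%.

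**7. Type I error.** On bounded data the ungated interaction test held 0.042–0.050 and the two-stage rule 0.046–0.051, with participants simulated as independent. The gate is not needed to protect α.

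**The case against.** The strongest reply is that the section only says data will be assessed, and that its fallback wording allows methods that keep the question intact. A mixed ANOVA on transformed scores still tests group-by-time, on the transformed scale, and still carries covariates. A rank-based ANCOVA also carries covariates. Naming the fallback could be left to an analysis plan that is not shown. All of this stands, and it confines the covariate and estimand problem to simple rank tests. It does not remove the gate, which this document fixes and which leaves those simple tests open.

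A reader might infer four stronger points that the text does not support:

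- **That no group-by-time test would be run after a rejection.** The mixed-effects models in the next paragraph carry no pre-test condition. They are not called primary, however, and their stated purpose is residual center effects.
- **That FMA-UE would usually be switched.** The rate depends on an unreported distribution and an unstated way of testing. At the low end of the cell-wise runs it is no higher than for normal data. The entry cut also concerns FMA-UE only, not the other three outcomes.
- **That power would be halved.** For the fallback test taken alone, this needs a post-score rank test and a correlation of about 0.8 or more. The two-stage rule on normal data loses less. At 0.5, the correlation that reproduces 42, nothing material is lost.
- **That raw values rather than residuals are tested.** This is a natural reading of the sentence, but it is not stated.

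**Conclusion.** The point holds in limited form. The protocol lets pre-tests choose each outcome's analysis, with an open-ended fallback, although the sample size was built on one specific test. Under a cell-wise, any-rejection reading, about 34% of perfectly normal outcomes would leave the planned ANOVA, and bounded FMA-UE data would do so at a similar or higher rate.

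The power consequence runs from none to a drop from about 0.80 to about 0.65. The lower end assumes Kruskal-Wallis on post scores, correlation 0.8, normal data and an effect on change held at the planned size. The harm is to comparability across outcomes and possibly to power, not to type I error from switching. These calculations leave aside any effect of having one center per arm, which is a separate matter. The change should be made because it removes the ambiguity at almost no cost.

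**What to change.** Delete the rule that Shapiro-Wilk and Levene results select the analysis. State instead that one pre-specified model is primary for every outcome whatever the distributional checks show: either the post score adjusted for baseline with group as a factor, or the group-by-time model the sample size assumed. Say how this model relates to the mixed-effects models in the next paragraph, so that only one is primary. Check its residuals graphically. Report a permutation test or a rank-based ANCOVA of the same group contrast as a sensitivity analysis.

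In the bounded-data simulations the ungated interaction test had power 0.64–0.80. Baseline-adjusted ANCOVA had 0.76–0.90 where post scores were generated by regression on baseline; that gain comes mainly from the adjustment rather than from dropping the gate.

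The cost is one rewritten paragraph and one additional analysis run, with no extra participants, visits or staff.

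### The promised covariate adjustment leaves the group-by-time effect unadjusted unless covariate-by-time terms are added, and the protocol does not say which model is meant

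*Protocol article*

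**What the plan says.** Under Statistical Analysis, for outcomes that meet parametric assumptions, "a 2-way mixed model ANOVA will be used to compare the effects" between and within groups. The same paragraph continues: "Potential confounding variables, such as baseline motor function and stroke severity, will be included as covariates to provide adjusted treatment effect estimates". No covariate-by-time term is mentioned. The next paragraph adds a linear mixed-effects model for the group-by-time interaction, with center as a fixed effect and a participant random intercept. It does not say whether the covariates belong in that model too.

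Under Assessment of Outcomes, a blinded assessor "will conduct baseline and postintervention assessments to prevent bias". These are the only two time points, so the baseline score is one of the two responses in a group-by-time model.

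Under Sample Size Calculation, the planned test is the "ANOVA repeated measures within and between interactions" option: "With a study power of 80%, an α level of .05, and an effect size of 0.25", from which "a minimum sample size of 42 participants (14 in each group) is required". Recruitment and Randomization assigns one center to each arm.

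**The concern.** With two time points, group by time is the difference between arms in mean change from baseline. The protocol promises to adjust this effect for baseline motor function and stroke severity. Whether any adjustment takes place depends on a model term that the text does not mention.

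As main effects, the covariates leave the estimate where it was, and the report would present as adjusted a figure that is not. An outcome's own baseline would also be both response and covariate, which understates the standard error in a random-intercept model. With covariate-by-time terms, the estimate, the standard error and possibly the conclusion change. If this is left open, the choice could be made after the data are seen. Only three centers are allocated, so baseline differences between arms are likely and the choice is not academic.

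**Working it through.** **Inputs.** From the protocol: N = 42 (14 per arm), k = 3 arms, m = 2 assessments, f = 0.25, α = 0.05. Assumed because not stated: pre-post correlation ρ, and sphericity (automatic with two time points). All data sets below are simulated, not trial data.

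**1. The plan's own figure.** For the interaction, λ = f²·N·m/(1−ρ) = 0.0625 × 42 × 2/0.5 = 10.5, with 2 and 39 degrees of freedom. Power is 0.803, and 42 is the smallest multiple of 3 that reaches 80%. The stated N is thus reproduced at ρ = 0.5. Other values do not give it: ρ = 0.3 needs 60, 0.6 needs 36, 0.7 needs 27.

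**2. Covariates as main effects.** If y at each visit contains γx for a time-constant x, then γx cancels in post minus baseline.
- Severity-type covariate, one data set: interaction estimates 0.4717 and 0.3606, SE 0.4215, both without and with the covariate.
- Outcome's own baseline, another data set: estimates 2.365 and 4.629 both without and with it. The random-intercept variance falls from 13.7 to about 0 and the SE from 1.97 to 1.78.

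**3. Size of the standard error fault.** Take unit variances. With baseline b on both sides, the pooled slope is (1+ρ)/2. The residuals at the two visits then have covariance −(1−ρ)²/4, which is negative, so the intercept variance is estimated at zero. The pooled residual variance is (1−ρ)(3+ρ)/4.
- Model variance of an arm contrast: (1−ρ)(3+ρ)/n. True variance: 4(1−ρ)/n. Ratio: (3+ρ)/4.
- ρ = 0.5: ratio 0.875, SE ratio √0.875 = 0.935. The 5% critical value of F(2, 39) is 3.238, and 3.238 × 0.875 = 2.833. The tail probability is (1 + 2 × 2.833/39)^(−19.5) = 0.071.
- ρ = 0.7: ratio 0.925, type I error 0.062.
- Separate simulations gave 7.1% to 7.5% at ρ = 0.5 and 6.2% to 6.6% at ρ = 0.7.

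**4. Baseline with its time interaction.** In the second data set of step 2, the repeated-measures interaction test with baseline-by-time gives F = 4.312, p = 0.0205. ANCOVA on the post score gives the same F and p, with arm estimates 0.823 and 4.306. The unadjusted change test gives F = 2.762, p = 0.076. One sentence in the protocol thus covers two different results.

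**5. Power under ANCOVA.** The error variance 1−ρ² replaces 2(1−ρ), so λ is multiplied by 2/(1+ρ). At ρ = 0.5, λ = 10.5 × 2/1.5 = 14.0 with 2 and 38 degrees of freedom, and power is 0.906 (simulated 0.900, against 0.800 unadjusted). Holding the change-score test at λ = 10.5 for other ρ:

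| ρ | ANCOVA power |
|---|---|
| 0.3 | 0.943 |
| 0.5 | 0.906 |
| 0.6 | 0.886 |
| 0.7 | 0.866 |
| 0.8 | 0.845 |
| 0.9 | 0.824 |

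**6. Center differences.** Assume no treatment effect, a 0.5 SD spread between the extreme center means at baseline, and ρ = 0.5.
- Differences that persist to the post score: the change contrast is unbiased, and ANCOVA is off by (1−ρ) × 0.5 = 0.25 SD. Simulated type I error is 4.9% for change and 8.9% for ANCOVA.
- Differences that vanish by the post score: change is off by 0.5 SD and ANCOVA by ρ × 0.5 = 0.25 SD. Simulated type I error is 19.3% and 9.3%.

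**The case against.** The strongest reply is that the adjustment can work as planned. The covariate sentence sits in the mixed ANOVA paragraph, nothing there excludes covariate-by-time terms, and with them the test is exactly ANCOVA. A reader might infer from step 2 that the stated adjustment is impossible; the documents do not support that. What stands is that the sentence covers both a model that adjusts and one that does not. Because the protocol makes a positive promise of adjusted estimates, this is more than detail that an article may leave out.

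A reader might also infer that the protocol's linear mixed model has an inflated error rate because of baseline. The text lists only center and the participant intercept for that model and does not expressly place the covariates there. The 7% figure applies only if an outcome's own baseline is added as a main effect.

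Third, baseline motor function need not be each outcome's own baseline: Table 3 attaches motor function to the Wolf Motor Function Test. For the other outcomes the double use may not arise. A main-effect covariate would still adjust nothing there.

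Finally, ANCOVA is not clearly better when three centers are randomized, one per arm. This is right as far as it goes: step 6 shows it worse than the change contrast under persistent center differences and better when they fade. It is a reason to report both. It does not justify leaving unspecified an adjustment to which the protocol already commits.

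**Conclusion.** The point holds as a fault of specification. Entered as main effects, the named covariates leave the group-by-time estimate unadjusted; entered with time interactions, they give ANCOVA. The protocol's wording allows either.

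The standard error fault is small (about 6% too small at ρ = 0.5, 4% at ρ = 0.7) and conditional on the model described in step 3.

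The nominal gain from a working adjustment is 80% to about 91% at ρ = 0.5. With the change-score test held at 80%, ANCOVA gives about 87% at ρ = 0.7 and 82% at ρ = 0.9. A reader might take 91% as the power this trial would have. The documents do not support that: ρ is only implied by the sample size, and the calculation treats 42 participants as independent although arm and center coincide. The case for the change rests on making the promised adjustment real and unambiguous; the gain in power is secondary and is no remedy for the single-center-per-arm design.

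**What to change.** For each outcome, define the adjusted analysis as an ANCOVA of the postintervention score on arm and the baseline score of the same instrument, with arm contrasts and confidence intervals. Adding baseline-by-time to the mixed ANOVA is equivalent. Put stroke severity, or any other covariate named in advance, in that same model. State that baseline is not to be used both as a response and as a main-effect covariate.

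Report the unadjusted group-by-time contrast beside it, and say that the two are to be read together because center differences can favor either. State the pre-post correlation assumed in the sample size calculation. Say plainly that the adjustment does not separate arm from center.

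The cost is a few sentences of analysis wording and one degree of freedom for baseline (39 to 38), plus one for each further covariate. The data and software stay the same.
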